### Statistical Analyses

#### Descriptives

We will describe the sample by calculating means and frequencies across demographic variables such as gender. We will also calculate mean scores on the DSM-5-CCSM to describe presenting mental health across 12 psychiatric domains. We will report internal consistency estimates and correlations between all measures to provide an indication of their reliability and convergent validity in the sample, given a lack of prior validation with Indigenous samples. With respect to app use among the intervention group, we will calculate the average frequency and duration of app use both in general and for each feature.

#### Primary Outcome

We will calculate the change in overall emotion regulation using the DERS-SF total score and the change in specific domains via the DERS-SF subscale scores. An independent statistician will use linear mixed modeling to test whether the change in emotion regulation is greater for those in the intervention condition relative to those in the control condition by including an interaction term between time and group [61]. We will evaluate the final sample to determine whether it is also feasible to analyze gender and baseline mental health symptoms as subgroup effects via interaction terms [62,63]. Analyses will be conducted with an intent-to-treat approach. Missing data will be handled with full information maximum likelihood estimation, which is recommended for avoiding bias in parameter estimates [64,65].

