**Intervention (UP+JoyPop; or UP only)**					
	Outcomes measured: emotion regulation, mental health, treatment readiness, and service usage		✓	✓	✓
	Outcome measured: app quality				✓—intervention group only
	Control group participants given access to app				✓

Following consent, participants will complete the baseline assessment measures. They will be encouraged to respond as honestly and accurately as possible and not how they think researchers might want them to. Any participant that endorses suicidal thoughts during the first assessment will see an onsite counselor who will conduct a risk assessment and intervene as needed. Following completion of the assessment measures, the research assistant will access the allocation envelope from the locked filing cabinet, open it to determine the allocation, inform the participant, and proceed with associated study tasks. Participants allocated to the intervention condition will be supported in accessing and learning about the app. All participants will return to Dilico after 2 and 4 weeks to complete the second and third assessments. Once they have finished the study at the end of their third assessment, participants in the control condition will learn about and receive access to the app.

To promote retention, participants will receive reminders about upcoming assessments via text and email. To incentivize completion [42,43], participants will receive cash compensation (CAD $20 [US $13.89] for baseline assessment; CAD $25 [US $17.36] for second assessment (after 2 weeks); CAD $30 [US $20.83] for third assessment (after 4 weeks); and an additional CAD $25 [US $17.36] if all assessments are completed). We will arrange transportation (taxis, bus fare) if required for participants. Promising retention rates were observed using these methods in a pilot study [44].

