#### Secondary Outcomes

We will calculate change in mental health using total scores from the DASS-21 and SDQ, while we will calculate change in specific domains using the DASS-21 and SDQ subscale scores. We will calculate change in treatment readiness using the treatment readiness subscale from the MYTS as described. Similar to the primary outcome analyses, linear mixed modeling will be used to test whether the change in mental health symptoms and treatment readiness is greater for those in the intervention condition relative to those in the control condition by including an interaction term between time and group [61]. Covariates of gender and baseline mental health symptoms will again be included. With respect to service usage, we will estimate the costs of services used among participants in each condition and conduct a cost-consequence analysis to determine the incremental costs or savings associated with receiving the app [66].

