#### Sample Size

We calculated the required sample size for a 2 (between subjects; treatment condition) by 3 (within subjects; time) mixed design, roughly estimating the statistical power needed for the planned linear mixed model for the primary outcome under the assumption of compound symmetry. We used parameters of *f*=0.2 (small to medium effect), =0.05, and power=0.95, resulting in a suggested sample size of 66 to achieve necessary power. We estimate 60% retention throughout the study (40% attrition) based on our initial research [53]; as such, an initial sample of 110 will be recruited.

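### Free improvement: constraining the arms' baseline means to be equal, or adjusting for each scale's own baseline, would make the planned time-by-group test more precise at no cost in data

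*Protocol article*

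**What the plan says.** Under Statistical Analyses, Primary Outcome, a linear mixed model tests whether DERS-SF change is greater in the intervention arm "relative to those in the control condition by including an interaction term between time and group". Secondary Outcomes uses the same test for the DASS-21, SDQ and treatment readiness. The Outcomes section defines the outcome as change from baseline to weeks 2 and 4.

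The Sample Size section refers to a "2 (between subjects; treatment condition) by 3 (within subjects; time) mixed design", offered as a rough power estimate for the planned mixed model "under the assumption of compound symmetry". The three times are baseline, week 2 and week 4, so baseline is one of the outcome levels.

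On covariates, Primary Outcome considers gender and baseline symptoms only as subgroup interactions, and only if the final sample allows. Secondary Outcomes then says: "Covariates of gender and baseline mental health symptoms will again be included". It does not say whether they enter as main effects or by time.

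On timing, Study Procedure says: "Following completion of the assessment measures, the research assistant will access the allocation envelope from the locked filing cabinet". The baseline scores therefore exist before anyone knows the arm.

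The article does not name the scale's own baseline as a covariate or state a common baseline mean. It also does not say in words that the group difference at baseline is freely estimated.

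**The concern.** When baseline is an outcome row and each arm has its own baseline mean, the time-by-group term is a difference between arms in change scores. Randomisation after the baseline assessment makes the expected baseline means equal. The baseline group parameter then estimates a quantity known to be zero, and its sampling error passes into the contrast of interest. A model that uses the known equality gives the same estimand with smaller variance.

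Precision is at stake on the primary scale and on every secondary scale analysed the same way. Gender and baseline symptoms, in whatever form they enter, do not replace the scale's own baseline.

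**Working it through.** **Inputs from the article.** Two arms, three times, f=0.2, alpha 0.05, compound symmetry, 1:1 allocation; "and power=0.95, resulting in a suggested sample size of 66"; 40% attrition; 110 recruited.

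**Assumptions.** ρ is not stated. The shape of the effect over time is not stated; I take linear growth, or an immediate and sustained effect. Week-2 loss is not stated; I take 20%. SD = 1.

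**1. Reproduce the plan's figure.** For the interaction, λ = f²·N·m/(1−ρ), with 2 and 2(N−2) degrees of freedom. At ρ=0.5 and N=66, λ = 0.04×66×3/0.5 = 15.84 and power is 0.9504. At N=64 power is 0.9439. So 66 reproduces, and 66/0.6 = 110. Other correlations do not give 66: ρ=0.4 needs 80 and ρ=0.6 needs 54. The figure is therefore the one for the free-baseline interaction test at ρ=0.5.

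**2. Week-4 contrast, complete data.** Up to the common factor 4/N:
- free baseline: 2(1−ρ)
- baseline means constrained equal, or own baseline adjusted: 1−ρ²
- ratio: (1−ρ²)/[2(1−ρ)] = (1+ρ)/2

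| ρ | 0.4 | 0.5 | 0.7 | 0.8 |
|---|---|---|---|---|
| ratio | 0.70 | 0.75 | 0.85 | 0.90 |

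For N=110 and ρ=0.5: (4/110)×1.00 = 0.03636 against (4/110)×0.75 = 0.02727.

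**3. With attrition.** With 110 randomised, 20% missing at week 2, 40% at week 4, random monotone dropout and ρ=0.5, the generalised least squares variance is 0.0535 free and 0.0444 constrained. The reduction is 1 − 0.0444/0.0535 = 17%, and the SE goes from 0.231 to 0.211.

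**4. Power at the planned effect.** At f=0.2 the week-4 difference is 0.2×√24 = 0.98 SD (linear, with 0.49 at week 2) or 0.2×√18 = 0.85 SD (sustained). For the 2-df test of both post-baseline differences, λ = (N/4)·d′S⁻¹d, with S = (1−ρ)[[2,1],[1,2]] free and (1−ρ)[[1+ρ,ρ],[ρ,1+ρ]] constrained. At N=66 and ρ=0.5:
- free: 16.5×0.96 = 15.84, power 0.950, either pattern
- constrained, linear: 16.5×1.32 = 21.78, power 0.990
- constrained, sustained: 16.5×1.44 = 23.76, power 0.994

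Put another way, 95% power needs 50 (linear) or 46 (sustained) completers instead of 66.

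**5. The listed covariates** (N=110, ρ=0.5, illustrative covariate correlating 0.6 with baseline, and 0.6 or 0.3 with later scores). Week-4 variance under a free baseline:

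| | Complete data | With dropout as in step 3 |
|---|---|---|
| no covariate | 0.0364 | 0.0535 to 0.0536 |
| main effect | 0.0364 (no change) | 0.0510 or 0.0542 |
| covariate by time | 0.0334 or 0.0367 | 0.0511 or 0.0516 |

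In these scenarios the gain ranges from none to about 8%. Once baseline is constrained, a by-visit covariate can add more: with complete data the variance goes from 0.0273 to 0.0224 if the covariate still correlates 0.6 with later scores, but shows no gain (0.0275) if that correlation falls to 0.3.

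**The case against.** The best reply is that free estimation at baseline is an inference. The Primary Outcome section says only that a time-by-group term is included, and a constrained-baseline model also tests such terms. The 2-by-3 layout appears in a self-described rough power calculation, and how baseline enters is a detail that a fuller plan may settle. This stands in part: the article does not exclude the better model. But the wording, the outcome defined as change, and a sample size that reproduces for the free-baseline test all point the same way, and nothing points the other way.

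It is also fair to say that nothing here is invalid. The planned test is unbiased under randomisation, and at the planned effect power is already 0.95 on the plan's own terms.

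Several stronger readings are tempting and are not supported:
- That baseline information is wasted. A change contrast already removes between-person variance; baseline is used, but not optimally.
- That the covariates can do nothing. This is true only of main effects with complete data. By-time terms, or the expected dropout, can give a small gain.
- That the plan gives false assurance about its covariates. The article never claims they add precision; for the primary outcome it considers them for subgroup effects.
- That baseline symptoms for the DASS-21 and SDQ are those scales' own first row. The Descriptive Measures section names the DSM-5-CCSM for baseline symptom presentation, and that is the natural referent.

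**Conclusion.** The point holds as a free improvement. On the natural reading, the primary and secondary mixed models use baseline less efficiently than randomisation allows.

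- **Complete data:** the week-4 variance is multiplied by (1+ρ)/2. That is 0.75 at the ρ that reproduces 66, and 0.70 to 0.90 over the assumed 0.4 to 0.8.
- **Stated 40% week-4 loss, with 20% assumed at week 2:** about 17% less variance at ρ=0.5.
- **Power at f=0.2 with 66 completers and ρ=0.5:** from 0.95 to about 0.99, which is modest. The gain matters more if the true effect is smaller. A variance factor of 0.75 gives about the same week-4 power for a difference √0.75 = 0.87 times as large.

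A reader might infer that the trial is underpowered for its stated effect because of this choice. The documents do not support that: 66 and 110 reproduce. The sizes rest on compound symmetry, which the article assumes, and on ρ, the week-2 loss and the effect pattern, which it does not give.

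**What to change.** For each scale, state one of two models:

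- **Constrained longitudinal model:** baseline, week 2 and week 4 as outcomes, categorical visit, one common baseline mean, group terms only at weeks 2 and 4, unstructured covariance.
- **Baseline-adjusted model:** weeks 2 and 4 as outcomes, with that scale's own baseline by visit as covariate.

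The first keeps everyone with a baseline score in the likelihood and so sits more easily with intent-to-treat. Enter any other covariate meant for precision with its interaction with visit, and say in the Secondary Outcomes section what form gender and baseline symptoms take. Keep full information maximum likelihood and intent-to-treat.

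The cost is a sentence or two of analysis wording. It needs no new data and leaves the recruitment target of 110 as it is. The only added assumption is equal expected baseline means, which randomisation after the baseline assessment supplies. The article reports recruitment as ongoing and the statistician as blinded to condition, so the change can be fixed before results are known.

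### Full information maximum likelihood, taken literally and without a small-sample correction, puts the type I error of the primary time-by-group test modestly above 0.05

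*Protocol article*

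**What the plan says.** The Primary Outcome section of the analysis plan tests the DERS-SF in a linear mixed model "by including an interaction term between time and group". After an intent-to-treat statement it adds: "Missing data will be handled with full information maximum likelihood estimation, which is recommended for avoiding bias in parameter estimates". It does not mention REML, a test statistic or a degrees-of-freedom method.

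The Secondary Outcomes section does not repeat the estimator. It says only that "Similar to the primary outcome analyses, linear mixed modeling will be used" for mental health symptoms and treatment readiness.

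The Sample Size section sizes the trial as a "2 (between subjects; treatment condition) by 3 (within subjects; time) mixed design", "under the assumption of compound symmetry", with f = 0.2 and "0.05, and power=0.95, resulting in a suggested sample size of 66 to achieve necessary power". With 60% retention, 110 are to be recruited.

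**The concern.** The reason given for the estimator is that it avoids bias. Under missing-at-random that is true of the mean parameters, which is what matters for handling missing data. It is not true of the variance parameters. Maximum likelihood divides the residual sum of squares by the number of observations without subtracting the degrees of freedom used for the means, so the variances, and with them the standard errors, come out too small. If the statistic is then compared with a chi-square or normal distribution, the uncertainty in the estimated covariance is ignored as well. Both errors act in the same direction.

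REML is also a direct-likelihood method. It uses the same incomplete records under the same assumption, so nothing in the missing-data strategy requires the unrestricted version. At stake is whether the test behind the superiority claim holds the 0.05 level used to size the trial.

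**Working it through.** **Inputs.** From the Sample Size section: 2 groups, 3 assessments, f = 0.2, alpha 0.05, power 0.95, compound symmetry, 66 after attrition, 60% retention, 110 recruited. Allocation is 1:1 (Randomization and Blinding). Assumptions not in the document: correlation between assessments 0.5, normal data, time as a categorical factor (2-df interaction) and no covariates. For the simulations, dropout is monotone and completely at random, with 88 people seen at 2 weeks.

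**Step 1: the plan's own figures.** For the interaction, the noncentrality is λ = f²·N·m/(1 − ρ), with df1 = 2 and df2 = 2(N − 2). At N = 66, m = 3 and ρ = 0.5, λ = 0.04 × 66 × 3/0.5 = 15.84 with df2 = 128, and the power is 0.9504. The figure of 66 is reproduced. It depends on the correlation: ρ = 0.3 would need 92 and ρ = 0.7 would need 42. Attrition: 66/0.6 = 110, also reproduced.

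**Step 2: variance bias.** With complete data under compound symmetry, maximum likelihood divides the within-person sum of squares by 2N, and REML divides it by 2(N − 2). The ratio is (N − 2)/N.
- N = 66: 64/66 = 0.970, understated by 3.0%.
- N = 110: 108/110 = 0.982, understated by 1.8%.

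**Step 3: exact type I error, complete data, compound symmetry.** The REML F statistic has an exact F(2, 2(N − 2)) distribution under the null. Each other test rejects when that F exceeds a lower cut-off:
- ML, Wald chi-square: (5.991/2)·(N − 2)/N, which is 2.905 at 66 and 2.941 at 110.
- ML, likelihood ratio: (exp(5.991/(2N)) − 1)·(N − 2), which is 2.972 and 2.982.
- ML with an F reference: the F critical value times (N − 2)/N, which is 2.974 and 2.982.
- REML, chi-square: 5.991/2 = 2.996.

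| Test | N = 66 | N = 110 |
|---|---|---|
| ML, Wald chi-square | 5.84% | 5.49% |
| ML, likelihood ratio | 5.48% | 5.28% |
| ML, F reference | 5.46% | 5.28% |
| REML, chi-square | 5.35% | 5.21% |
| REML, F reference | 5.00% | 5.00% |

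**Step 4: exact type I error, complete data, unstructured covariance.** The ML Wald statistic equals 2N/(N − 3) times an F(2, N − 3) variable. The rate is P(F(2, N − 3) > 5.991(N − 3)/(2N)), which is 6.5% at 66 and 5.9% at 110. REML with the same chi-square reference still gives 6.0% at 66.

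**Step 5: simulated type I error with dropout from 110 to 88 to 66.** There were 20,000 null trials per setting, with a Monte Carlo standard error of about 0.16 to 0.18 percentage points. The F references used 108 or 64 denominator degrees of freedom.

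| Covariance | Estimator | Chi-square | F reference |
|---|---|---|---|
| Compound symmetry | ML | 5.9% | 5.1–5.4% |
| Compound symmetry | REML | 5.4% | 4.8–5.0% |
| Unstructured | ML | 6.7% | 5.9–6.2% |
| Unstructured | REML | 6.2% | 5.5–5.8% |

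**Step 6: how much is due to the estimator.** With the chi-square reference held fixed, using ML instead of REML adds 5.84 − 5.35 = 0.49 points at 66 and 5.49 − 5.21 = 0.28 points at 110. With dropout it adds about 0.4 points under either covariance. The rest of the excess comes from the reference distribution and, in the larger figures, from the unstructured covariance.

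**The case against.** The strongest reply is that the sentence concerns missing data. It says that incomplete participants stay in the analysis through direct likelihood, and that is sound. The error rate depends on the test statistic, the degrees of freedom and the covariance structure. The article states none of these for the analysis, and a condensed article may leave them to an analysis plan that is not shown. This stands in part: the silence on those items is not itself a fault, and an analyst could still apply a small-sample method. What remains is that the one estimator named is, read literally, unrestricted ML, and that avoiding bias is given as its merit.

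A reader might infer several stronger things that the document does not support.
- **That the estimator alone causes the inflation.** It accounts for roughly 0.3 to 0.5 percentage points.
- **That the true level is 6.5% or more.** That requires an unstructured covariance and a chi-square reference. The only structure the protocol names is compound symmetry, and it names it for sizing.
- **That the level is far off because recruitment is slow.** Two participants had completed by July 2024, and the excess would grow in a much smaller trial. But no such size is planned, and severe under-recruitment would be a problem of power and feasibility, not an error in this sentence.
- **That every secondary test is affected.** The Secondary Outcomes section calls its models similar but does not name the estimator, so this is only implied.

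**Conclusion.** The point holds, and it is minor. If the primary model is fitted by unrestricted ML without a small-sample correction, the 2-df test exceeds its nominal level by about 0.3 to 0.8 percentage points with complete data under compound symmetry. The excess reaches about 1.7 points in the worst case examined (unstructured covariance, expected attrition, chi-square reference). The protocol gives the overall attrition but not its split between visits, and it fixes neither that covariance nor that reference. The dropout figures also rest on correlation 0.5, normal data, dropout completely at random and 88 people at 2 weeks. The calculated 66 and the recruited 110 are unaffected.

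**What to change.** In the Primary Outcome section, replace the sentence on full information maximum likelihood with a statement along these lines: the linear mixed model will be fitted by restricted maximum likelihood to all available assessments, under missing-at-random, with F or t tests and Kenward-Roger (or Satterthwaite) degrees of freedom. The sources now cited for full information maximum likelihood should be kept only if they support the new wording. In the Secondary Outcomes section, say that the same estimation and testing rules apply.

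Both parts are needed, because REML with a chi-square reference leaves some of the excess. Under compound symmetry with complete data, REML with the F reference gives exactly 5.0%. Kenward-Roger itself was not simulated under the expected attrition, so an exact 5.0% should not be promised there.

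The cost is a sentence in each section, a software option and slightly larger p-values. Intent-to-treat, the missing-data assumption and the sample size do not change.

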#### Secondary Outcomes

We will calculate change in mental health using total scores from the DASS-21 and SDQ, while we will calculate change in specific domains using the DASS-21 and SDQ subscale scores. We will calculate change in treatment readiness using the treatment readiness subscale from the MYTS as described. Similar to the primary outcome analyses, linear mixed modeling will be used to test whether the change in mental health symptoms and treatment readiness is greater for those in the intervention condition relative to those in the control condition by including an interaction term between time and group [61]. Covariates of gender and baseline mental health symptoms will again be included. With respect to service usage, we will estimate the costs of services used among participants in each condition and conduct a cost-consequence analysis to determine the incremental costs or savings associated with receiving the app [66].

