### Outcomes

The primary outcome is change in emotion regulation from the baseline assessment to the second assessment (after 2 weeks) and to the third assessment (after 4 weeks). Secondary outcomes are changes in mental health symptoms, readiness for treatment, and service usage from the baseline assessment to the second assessment and to the third assessment.

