Service usage will be assessed with 5 items generated by the research team that ask respondents how many times they accessed various health care services (ie, walk-in clinic, family doctor or nurse practitioner, emergency department, mental health counselor, and mental health hotline or phone support) over the previous 2 weeks.

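### Service use is defined as change from baseline, but its only stated analysis compares costs per arm with no role for the baseline count; adjusting for that count would fix the mismatch and gain precision at no cost

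*Protocol article*

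**What the plan says.** All places are in the protocol article.

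- **Outcomes** groups service usage with the outcomes defined as changes: "Secondary outcomes are changes in mental health symptoms, readiness for treatment, and service usage from the baseline assessment to the second assessment", and likewise to the third assessment.
- **Table 1** schedules service usage at T1 (baseline), T2 (2 weeks) and T3 (4 weeks): "Outcomes measured: emotion regulation, mental health, treatment readiness, and service usage".
- **Secondary Outcome Measures** gives five count items, each with a recall period stated as "over the previous 2 weeks".
- **Study Procedure** puts allocation after the baseline forms: "Following completion of the assessment measures, the research assistant will access the allocation envelope from the locked filing cabinet". The T1 count therefore lies wholly before randomisation, while the T2 and T3 forms together cover the 4 trial weeks.
- **Statistical Analyses, Secondary Outcomes** applies the time-by-group mixed model to mental health symptoms and treatment readiness. The covariates named there are gender and baseline symptoms. Service usage is handled separately: "we will estimate the costs of services used among participants in each condition and conduct a cost-consequence analysis". The stated aim is "to determine the incremental costs or savings associated with receiving the app".

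The Abstract makes the same split, with mixed models for change in outcomes and a cost-consequence analysis for service use.

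**The concern.** The outcome is a change, while the analysis is a cost per arm. Take a participant with 2, 1 and 1 visits at T1, T2 and T3. The defined outcome is -1 and -1, whereas use during the trial is 2 visits. The analysis text does not connect these two quantities and gives the T1 count no function.

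This matters because the second secondary objective asks whether the app reduces other service use and cost, and the Discussion says that demonstrated cost-effectiveness would support adopting the app into routine waitlist practice. Service use typically differs widely between people. With few completers per arm, each participant's own earlier use is the most direct means of removing some of that spread, and it is already being collected.

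**Working it through.** **Number available.** The Sample Size section states f = 0.2, power 0.95, 66 analysed and 110 recruited. Alpha is read as 0.05, since its symbol is lost in the text. For the interaction in a 2 x 3 design with an assumed within-person correlation of 0.5 (not stated), the noncentrality is 66 x 0.2² x 3 / (1 - 0.5) = 15.84 on 2 and 128 df. Power is then 0.9504, so 66 is reproduced. Recruitment is 66 / (1 - 0.40) = 110. With 1:1 allocation, 66 / 2 = 33 completers per arm. These figures concern the primary outcome; the article gives none for service use or cost.

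**Variance of each candidate analysis.** Assume three 2-week windows with equal variance (set to 1) and a common correlation ρ. The per-person variances are:

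- follow-up only (T2 + T3): 2(1 + ρ)
- change (T2 + T3 - 2 x T1): 6 - 6ρ
- follow-up adjusted for T1: 2(1 + ρ) - (2ρ)²
- all three windows summed: 3 + 6ρ

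| ρ (assumed) | Follow-up only | Change | Adjusted | SE ratio, follow-up only / adjusted |
|---|---|---|---|---|
| 0.2 | 2.40 | 4.80 | 2.24 | 1.04 |
| 0.3 | 2.60 | 4.20 | 2.24 | 1.08 |
| 0.5 | 3.00 | 3.00 | 2.00 | 1.22 |
| 0.7 | 3.40 | 1.80 | 1.44 | 1.54 |
| 0.8 | 3.60 | 1.20 | 1.04 | 1.86 |

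For example, at ρ = 0.5, √(3.00 / 2.00) = 1.22.

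**Change score against the others.** Change has a smaller variance than follow-up only when 6 - 6ρ < 2 + 2ρ, that is, when ρ > 0.5. Change minus adjusted is 4 - 8ρ + 4ρ² = 4(1 - ρ)², which is never negative. The change score therefore never beats adjustment.

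**In terms of power.** Set the effect so that the adjusted analysis has 80% power at 33 per arm. At ρ = 0.3, 0.5 and 0.7:

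- follow-up only: 74%, 63%, 45%
- change: 53%, 63%, 71%

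**If T1 were summed in.** The standard error would be 1.46, 1.73 or 2.24 times the adjusted one at the same correlations. The expected absolute difference would not move, because T1 precedes allocation. A percentage reduction would fall to two thirds of its value, for example 2 x 30% / 3 = 20%.

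**Simulation check.** This used 20,000 trials with 33 per arm, overdispersed counts, an assumed mean of 1.5 visits per window and a 30% reduction. The true 4-week difference is 2 x 1.5 x 0.3 = 0.90 visits.

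| Analysis | Mean difference | SE |
|---|---|---|
| Follow-up only | -0.905 | 0.747 |
| T1 summed in | -0.909 | 1.118 |
| Change | -0.897 | 0.738 |
| Adjusted for T1 | -0.882 | 0.568 |

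The mean difference is essentially the same under all four. The adjusted estimate falls 0.018 short of the true value, which is small against its standard error. What separates the analyses is precision: 0.747 / 0.568 = 1.32.

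**The case against.** The strongest reply is that a journal article condenses the full protocol, so the costing window, covariates and interval method may be set out in a document not shown. That stands for the window taken alone, whose absence is no finding. It does not remove the difference between how the article defines the outcome and how it says it will analyse it.

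A second reply is that follow-up-only costing is valid and that the size of the gain rests on assumed correlations. This also stands. Emergency visits or hotline calls in 2-week windows may be sparse and weakly correlated, and at ρ = 0.2 the standard error ratio is only 1.04. The article sets no power target for service use.

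A third reply is that one clause reporting change in counts by arm would reconcile the two sections without redefining the outcome. It would, but it is less precise than adjustment at any correlation below 1, and below 0.5 it is less precise than follow-up costs alone.

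A reader might also infer something stronger: that the baseline form will be added into the total, and that the estimated saving will be diluted as a result. The documents do not support this. The analysis text neither sums T1 in nor says that it will be ignored. Costing services by condition to find savings from receiving the app points most naturally to the period after allocation. Even if T1 were included, the absolute difference, which is how the stated incremental costs or savings are most naturally read, would keep the same expectation. Only noise would be added, and only relative or standardised differences would shrink.

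**Conclusion.** The mismatch is real: service use is defined as change from baseline, and the one analysis stated for it contains neither change nor baseline. The consequence is lost precision and uncorrected chance imbalance, not bias. With about 33 completers per arm, a follow-up-only cost comparison has a standard error about 1.08, 1.22 or 1.54 times the baseline-adjusted one at correlations of 0.3, 0.5 or 0.7. Put the other way, adjustment cuts the standard error by about 7%, 18% or 35% (1 - √(2.24/2.60), 1 - √(2.00/3.00), 1 - √(1.44/3.40)).

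These figures assume equal variances and a common correlation across windows; the article gives no variance, visit rate or correlation for service use. The point is a worthwhile improvement that costs nothing to make. It does not show that the planned comparison would give a wrong answer.

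**What to change.** In Statistical Analyses, Secondary Outcomes, state that the cost-consequence analysis costs the two post-allocation windows (the T2 and T3 forms). State also that the arm difference in service counts and in cost is estimated with the participant's own T1 count or cost as a covariate, for example by regression with bootstrap intervals. In Outcomes, define the service-use outcome to match: use over the 4 weeks after allocation, adjusted for baseline use.

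This takes one or two sentences of analysis wording and a matching edit to the definition. It needs no new data, visits or participants. The article reports two completers as of July 2024 with recruitment ongoing, so at that point the wording could still be settled well before analysis.
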